Wichmann *et al* calculated an expansion factor for children by comparing data from three cohort studies to national surveillance data in Southeast Asia.^33^ For children in Thailand, the age-specific expansion factors calculated were 11.85 for <5 years, 8.76 for 5–9 years and 7.81 for 10–14 years.^33^ The results show that, even for Asia where better reporting and surveillance systems are available, there is a considerable degree of under-reporting. For Africa, there may be more dengue cases under-ascertained (not seeking care) and under-reported (not reported even if a patient with dengue seeks care, given that dengue is not one of the routinely notifiable diseases in Africa), but such information on the extent of underestimation of dengue was not available.^34 35^ Also, the incidence estimates used in our sample size calculations were not from population-based studies. While it would have been ideal to adjust the incidence further for likely underestimation, the annual incidence used in sample size calculations could not be adjusted for possible under-reporting due to the lack of data. The sample sizes were calculated with 95% confidence levels and a margin of error at a fixed significance level within 25% of the true proportion of incidence. This gives relative precision of 75%, considering the gap in evidence for dengue incidence in the study areas. The final sample sizes were calculated by assuming 10%–20% (variable by site) non-response rate or loss to follow-up. The required catchment population size for the fever surveillance study in Burkina Faso was estimated to be 100 000, Gabon to be 77 000 and Kenya to be 70 000. In these catchment populations, the number of enrolled subjects depends on the number of eligible patients who seek care at the study facilities. How many eligible febrile episodes would actually present at our study facilities was difficult to predict; but after assessment of the volume of febrile patients at the facilities, a realistic upper limit for enrolment for a study period of approximately 1.5 years was set at 3000 subjects to offer enrolment to all consenting eligible patients.

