### Study components

#### Fever surveillance—design and methods

To determine burden due to symptomatic dengue in each of the three sites in Burkina Faso, Gabon and Kenya, passive facility-based fever surveillance was implemented in a well-defined catchment area population. In Burkina Faso, the surveillance study was initiated in December 2014 in five selected primary healthcare centres, locally called ‘Centre de Santé et de Promotion Sociale’, in the municipality of Ouagadougou, with a catchment population of 105 000 residents. This project was implemented in collaboration with Centre Muraz in Bobo-Dioulasso, EQUITE sante programme (a collaborative programme between University of Montreal and Action-Gouvernance-Integration-Reinforcement, AGIR, based in Ouagadougou, funded by the Canadian Institute of Health Research) and DVI. In Gabon, the surveillance study was initiated in the ASH serving a catchment population of 130 000 residents in the Moyen-Ogooué and surroundings within Lambaréné, in collaboration with CERMEL and Institute of Tropical Medicine in Tubingen, Germany. In Kenya, the surveillance study was implemented at Ganjoni dispensary, Tudor subcounty Hospital and Coast Provincial General Hospital, serving a catchment population of 70 000 residents in Mombasa, in collaboration with Kenya Medical Research Institute and Ministry of Health of Kenya.

As described in figure 5, both outpatients and inpatients at the designated study facilities, who meet inclusion criteria as mentioned earlier were tested for dengue, first with SD Dengue Duo RDT. Dengue confirmation was done by detection of dengue virus in serum samples using PCR as well as antidengue IgM and IgG antibodies in acute and convalescent serum by ELISA (SD Dengue IgM & IgG capture ELISA tests, Standard Diagnostics, Yongin-Si, Korea).^10 37^ Every consecutive patient meeting inclusion criteria was eligible for enrolment during the study period. Infants<1 year old were not included due to operational limitations, such as difficulty of infantile bleeding.

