**Figure 6 F6:**
[figure not shown]
Laboratory testing algorithm for dengue. Samples from subjects of the passive fever surveillance would follow these steps of the testing algorithm for confirmation of dengue. *Dengue Duo^®^test is performed on enrolled febrile patients to identify dengue cases for immediate follow-up of dengue-confirmed cases in the cost-of-illness survey. **Selected samples, including those that were found positive by IgM and NS1 on Dengue Duo^®^, as well as those positive by IgM and IgG capture ELISA, will be tested with RT-PCR.

After ELISA testing, samples were shipped to the International Vaccine Institute (IVI) in Korea. Samples with positive results by RDT or ELISA, as well as a small number of samples with negative results, undergo further testing by RT-PCR at the Clinical Immunology Laboratory of IVI. Four DENV serotype-specific real-time RT-PCR assays are used for laboratory confirmation of dengue and serotyping.^38^ The DENV 1–4 RT-PCR assays are carried out in 25 µL reaction mixtures containing 5 µL template RNA, TagMan Fast Virus 1-step mastermix (Applied Biosystems), 0.9 µM of each primer and 0.2 µM probe.^38^ Amplification and detection are performed in a StepOne Plus real-time PCR system, and the baseline and threshold are determined using the auto-baseline and threshold feature in StepOne Software V.2.2.2 (Applied Biosystems). Thermocycling parameters are as follows: reverse transcription at 50°C for 5 min, inactivation at 95°C for 20 s, followed by 45 cycles of fluorescence detection at 95°C for 3 s and annealing at 60°C for 30 s.^38^ A specimen is considered positive if target amplification is recorded within 40 cycles.

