Outcome	Outcome of this particular visit	Hospitalised, returned home or referral
Hospitalisation	Information collected only among hospitalised patients in the surveillance to record other severe signs and progression of illness	Admission and discharge diagnoses Presence of haemorrhagic signs or shock syndrome
Hospital charges	Expenses and hospital charges incurred by patient on the visit 1	Amount of the out of pocket payment by the patient or the family/or guardian Breakdown of the hospital charges (laboratory, medication, admission-related charges)
Final outcome	Outcome of the patient’s illness at the second visit	Final diagnosis given for the patient, outcome of illness Completion of study participation (early termination and the reason and so on)

ALT, Alanine AminoTransferase; AST, Aspartate aminotransferase; IPD, Inpatient department; OPD, Outpatient department; RDT, Rapid Diagnostic Test.

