### Planned statistical analysis

From the fever surveillance data, incidence of symptomatic dengue among patients that seek healthcare at the study facilities will be calculated. Age-specific incidence rates in all the children and adults will be determined by referring to the size and distribution of the general population of the study area at the time of surveillance as the denominator in calculation of the incidence of symptomatic dengue cases. Each person residing in the study area is assumed to contribute 12 months of person time to the denominator. Although the study areas all report a low migration rate, the in-migration is assumed to balance the out-migration of the population during the study period. Age-specific incidence of symptomatic dengue will be calculated by using age-specific denominators and the number of symptomatic dengue cases in eligible individuals as the numerator.

Using the data collected in the Healthcare Utilisation Survey, the proportion of febrile cases missed by the passive surveillance system will be determined. Then using the proportion, the numerator will be further adjusted in recognition of those missed fever cases from the study area, which could have been dengue. Also, comparison will be made between those that agreed to participate and those that declined participation among the eligible potential enrolees. The enrolment log, which records basic information obtained during the screening process of potential enrolees, will be reviewed. In addition to checking that our sample of febrile cases is representative of febrile patients of the general population in the catchment area, refusal rates will be determined based on information in the log. Then, the refusal rates will be used to adjust the numerator.

SPSS software will be used for analysis of the fever surveillance data. Multivariable logistic regression will be used to compare confirmed patients with dengue versus patients with non-dengue febrile in terms of symptomatic presentation, based on signs and symptoms collected from all patients with laboratory-confirmed dengue by serology and RT-PCR, adjusting for possible confounders, such as age, days since onset of fever, primary versus secondary infection, inpatient versus outpatient and so on. Differences in symptomatic complex of dengue fever (DF) (and DHF, if data allows) by age and serotype will be also determined using multivariable logistic regression.

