One potential source of bias in estimating the incidence of symptomatic dengue is under-ascertainment due to the community residents with relevant symptoms seeking care from other healthcare providers and facilities than the study facilities. As the study design remains passive surveillance, cases are ascertained only at our study facilities. By estimating the proportion of febrile patients seeking care elsewhere as well as refusal rates among the potential enrolees that were screened for eligibility criteria, the degree of febrile patients missed by the study can be determined. Inverse probability weighting will be used to account for these potential subjects missed by the surveillance as adjustments in incidence calculation. Also, depending on the transmission volume of dengue or other cocirculating diseases with onset of fever, there may be patients that are diagnosed with other diseases and ruled out for dengue. Furthermore, with respect to dengue diagnostics for our serological surveys, there are other circulating flaviviruses in Africa leading to challenges in identifying antibodies to past dengue infections. While our testing plan assesses for some flaviviruses, others known to circulate in Africa, such as Banzi and Usutu viruses, are not part of the testing plan.^48–50^ Due to resource limitations, serological testing will be limited to yellow fever virus, West Nile virus, Zika virus and Japanese Encephalitis virus as well as DENV 1–4. Therefore, in some cases, it may be difficult to determine prior exposure to DENV versus other flaviviruses based on serological data. This cross-reactivity may lead to overestimation of dengue force of infection.

In addition, the serosurvey and healthcare utilisation survey are conducted on a randomised subsample of the catchment area population and there may be limited generalisability of the data collected from these surveys. With unknown differences among those that agree to participate and those that do not agree, the data may not be representative of the general population of the study countries.

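### The incidence corrections omit enrolled patients who test negative on the acute sample and give no convalescent sample, so dengue cases among them go uncounted and incidence is biased low

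*Protocol article*

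**What the plan says.** All references are to the protocol article.

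- **Confirmation.** Under Fever surveillance—design and methods, confirmation uses PCR and also "antidengue IgM and IgG antibodies in acute and convalescent serum by ELISA". Under Study questionnaires, the convalescent visit takes place at the facility after 10–14 days or at home after 15–21 days.
- **Acute testing.** Under Fever surveillance—laboratory testing, the acute sample gets a rapid test for NS1 and IgM/IgG on day 1 and later an IgM/IgG ELISA.
- **RT-PCR.** The same section, after the Figure 6 legend, says: "Samples with positive results by RDT or ELISA, as well as a small number of samples with negative results, undergo further testing by RT-PCR".
- **Corrections to the numerator.** Planned statistical analysis gives two. For care sought elsewhere: "Then using the proportion, the numerator will be further adjusted in recognition of those missed fever cases from the study area". For refusal: "Then, the refusal rates will be used to adjust the numerator".
- **Weighting.** The Discussion names the same two sources, "By estimating the proportion of febrile patients seeking care elsewhere as well as refusal rates among the potential enrolees", and continues: "Inverse probability weighting will be used to account for these potential subjects missed by the surveillance as adjustments in incidence calculation".
- **Attrition.** Sample size computes the final figures "assuming 10%–20% (variable by site) non-response rate or loss to follow-up". Table 1, final outcome row, collects "Completion of study participation (early termination and the reason and so on". No analytic use of that item is stated for the fever surveillance. A comparison of completers with non-completers is planned only for the serosurvey.

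**The concern.** Both stated corrections concern people who never entered the surveillance: they went elsewhere or they declined. A third loss arises after enrolment. A patient seen early in the illness may be negative on every acute test and become detectable only on the second sample. If that patient does not return, the case is not found.

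The two corrections scale up whatever was found among enrolled patients, so a shortfall in that count carries through in the same proportion. The error is always downward, and the confidence interval does not reflect it. Its size depends on each site's return rate, and comparison across Burkina Faso, Gabon and Kenya is a stated aim.

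The symptom model is also exposed. It contrasts confirmed dengue with non-dengue febrile patients, and the article mentions no third category for patients whose status was never settled.

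**Working it through.** The article gives no figure for this loss, so there is none to reproduce. The check traces who can be confirmed and then sizes the loss.

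**Routes to confirmation for an enrolled true case**

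1. Positive on the acute rapid test or acute ELISA: goes to RT-PCR and can be identified without a second visit.
2. Negative on the acute tests, returns: can be found on the convalescent ELISA.
3. Negative on the acute tests, does not return: no paired serology, and no RT-PCR unless among the small number of negatives selected.

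Only route 3 is lost. Neither stated correction reaches it.

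**Inputs**

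- d, the share of enrolled patients without a convalescent sample: not given. I use 10%–20% from Sample size as an upper reading, because that allowance combines non-response with loss.
- s, the share of true cases detectable only on the convalescent sample: not given. Assumed 0.1–0.6, with 1.0 as the extreme.
- Missing the visit is taken as independent of dengue status, and the few PCR-tested negatives are ignored.

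**Formula:** counted/true = (1 − s) + s(1 − d) = 1 − d × s. The factor that restores the count is 1/(1 − d × s).

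| d | s | Understatement d × s | Restoring factor |
|---|---|---|---|
| 0.10 | 0.1 | 1% | 1.01 |
| 0.10 | 0.4 | 4% | 1.04 |
| 0.10 | 0.6 | 6% | 1.06 |
| 0.20 | 0.1 | 2% | 1.02 |
| 0.20 | 0.4 | 8% | 1.09 |
| 0.20 | 0.6 | 12% | 1.14 |

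The ceiling, at s = 1, is 10%–20%.

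**Between sites.** If s = 0.6 everywhere, but d is 10% at one site and 20% at another, the counted fractions are 0.94 and 0.88. Two sites with equal true incidence would then show a ratio of 0.88/0.94 = 0.94.

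**Which correction works**

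- Weighting only the convalescent-only cases by 1/(1 − d) gives (1 − s) + s(1 − d)/(1 − d) = 1, so the count is restored.
- Inflating the whole numerator by 1/(1 − d) gives (1 − d × s)/(1 − d). With d = 0.20 this is 0.98/0.80 = 1.23 at s = 0.1 and 0.88/0.80 = 1.10 at s = 0.6. That overstates incidence by 10%–23%.

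**The case against.** The strongest reply is that this is a condensed article. Rules for incomplete samples commonly sit in the full protocol or analysis plan, and the flow and testing figures are not visible here. The refusal adjustment is correct in itself. The home-visit option should limit missed visits, and PCR on some negatives is meant to exclude false-negative ELISA results. Even at the upper end, 12% is modest beside the planned 25% relative margin.

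Much of this stands as a limit on size and scope. It does not remove the point. The article does not leave the incidence adjustment open: it lists the corrections and ties the weighting to those two sources. The numerator counts dengue cases, so an unconfirmed case adds zero whatever label the patient receives. The 25% margin describes random error, whereas this error is systematic.

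Three stronger readings are tempting but not supported:

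- **That every patient who misses the second visit is lost to confirmation.** Those positive on acute NS1, IgM or ELISA can still be identified.
- **That the plan classifies acute-only negatives as non-dengue.** The article gives no classification rule for them, so their entry into that arm of the symptom model is a risk, not a stated choice.
- **That the symptom comparison is distorted because dengue cases are observed over a longer window.** Table 1 records signs at both visits, but the article does not say which visit's signs enter the model and gives no return rates by dengue status. Any odds ratio for this effect would rest wholly on assumed inputs.

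**Conclusion.** The point holds for one group: enrolled patients negative on the acute rapid test and ELISA who give no convalescent sample. The stated corrections omit them, and most get no RT-PCR, so true cases among them are not counted. Incidence is biased low by d × s, about 1%–12% for d = 10%–20% and s = 0.1–0.6.

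The direction follows from the plan as written, but the size does not. The range for s is assumed, d is an upper reading of a combined allowance, and independence of return and dengue status is assumed. A difference between sites follows only if return rates (or s) differ, and the article reports neither. A reader might infer that the whole 10%–20% is lost from the count. That would require that no case is ever detectable on the acute sample, contrary to the testing described. The matter should be settled before analysis, but it does not undermine the design.

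**What to change.** 1. Among acute-negative enrolled patients only, weight each case found on the convalescent sample by the inverse probability of having that sample, modelled on site, age group and days since fever onset. Count confirmed acute-positive cases without this weight.
2. Classify acute-negative patients with neither a convalescent sample nor a PCR result as indeterminate, and leave them out of the non-dengue group in the symptom model.
3. Fit the symptom model on visit 1 signs, so that both groups have the same window for recording signs.
4. Report convalescent completion by site and age group.
5. Give the incidence without the new weight as a sensitivity analysis and label it a lower bound with respect to this loss.

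The cost is analysis wording only. The Discussion already commits to inverse probability weighting, and Table 1 collects age, date of fever onset, test results and completion status. The downside is slightly wider intervals and a smaller non-dengue group.

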As outpatient disease accounts for the greater part of dengue disease burden, clinical profile of individuals with DENV infection will be characterised by the type of treatment (hospitalised vs outpatients) as well as by severity of the disease (severe vs non-severe by the 2009 WHO criteria).^46^ Classification is determined after the course of illness is completed (typically during the convalescent visit). Symptomatic dengue is classified as outpatient or hospitalised. Progression of dengue is recorded as DF, DHF I, DHF II, DHF III or DHF IV, and clinical patterns will be compared by the severity grade.^46 47^ These will be compared with results obtained from other DVI studies in Latin America (Colombia) and Asia (Thailand, Vietnam and Cambodia). Overall, comparisons will be made across Burkina Faso, Gabon and Kenya.

With the age-stratified sera that reflect the age distribution of the general population of the country, the serological survey sampling strategy ensures sufficient subjects to obtain precise age-specific estimates of seropositivity and seroconversion of the catchment area population. The seroconversion rate and change in the immune status will be determined by age group during the study period. The age-stratified serosurvey data will also allow calculation of the force of infection of dengue in the study population. After enrolment, there are subjects who drop out in the follow-up bleeds about 6 months later. Basic demographic information will be compared between those that completed participation and those with incomplete participation to check whether study subjects represent the catchment area population. Comparisons will be made among Burkina Faso, Gabon and Kenya.

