The present studies at three sites in Africa will provide important information on undocumented DENV circulation in Africa. Such data will help to strengthen the evidence base for dengue burden in Africa. Better defined disease burden data based on our studies could be used to assess the relative need for dengue prevention and control measures, such as whether a dengue vaccine would be a cost-effective public health intervention for countries in Africa. Clinical findings from our studies could also be used as a guide for dengue case detection and case management.

The studies have some important limitations. We recognise variability of dengue epidemiology over time and by region. Due to resource constraints, our studies are limited in terms of time frames and geographical extent. These constraints may limit the generalisability of our study results.

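### The dengue versus non-dengue logistic model adjusts for primary versus secondary infection, a status that non-dengue patients do not have

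*Protocol article*

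**What the plan says.** In the protocol article, Planned statistical analysis, the symptom comparison is set out in one sentence: "Multivariable logistic regression will be used to compare confirmed patients with dengue versus patients with non-dengue febrile in terms of symptomatic presentation", "adjusting for possible confounders, such as age, days since onset of fever, primary versus secondary infection, inpatient versus outpatient and so on". Both primary versus secondary infection and inpatient versus outpatient are therefore named for the contrast between dengue and non-dengue patients.

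The next sentence is a separate analysis among dengue cases: "Differences in symptomatic complex of dengue fever (DF) (and DHF, if data allows) by age and serotype will be also determined using multivariable logistic regression". Primary versus secondary status is not attached to it.

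On care setting, the article gives three descriptions. The same section says "Symptomatic dengue is classified as outpatient or hospitalised" and places that classification after the illness has run its course. Table 1 (Variables of the surveillance questionnaires) lists, as the outcome of the visit, "Hospitalised, returned home or referral". Table 1 also records, under basic information, whether the patient was enrolled in the inpatient or the outpatient department.

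**The concern.** A confounder must be able to take its values in both groups being compared. Primary or secondary status exists only once a patient has a dengue infection, so knowing that a patient has either value already tells us which group the patient is in. Entering it as an adjustment variable either destroys the comparison or changes what is estimated.

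At stake is the article's named method for comparing the presentation of dengue with that of other fevers. The Discussion says of the study more generally: "Clinical findings from our studies could also be used as a guide for dengue case detection and case management". It does not tie that use to this regression, but symptom odds ratios are an obvious input to it. Incidence, seroprevalence and force-of-infection estimates are not affected.

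**Working it through.** The article gives no effect size or power for this model, so there is no figure of its own to reproduce. The check is what each possible coding of the covariate does.

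**Inputs from the article.** Upper enrolment limit 3000 (Sample size). Dengue share 8.7%, the RDT-positive proportion (33/379) in an earlier Burkina Faso study (Site selection). Expected cases: 3000 × 0.087 = 261. The simulated draw had 268.

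**Assumptions, not in the article.** Half of dengue cases are secondary. The symptom occurs in 20% of non-dengue patients and 40% of dengue patients. Where primary and secondary cases differ, it occurs in 30% and 50%, which again averages 40%.

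**Dengue as the dependent variable**

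| Coding for non-dengue patients | Result |
|---|---|
| Missing, complete-case analysis | 268 patients kept, 0 non-dengue; no comparison |
| Third level, not applicable | Complete separation: singular matrix in one routine; in another, symptom coefficient about 0 with standard error about 16,000 |
| Coded 0 (not secondary) | Quasi-separation: covariate coefficient about 28, standard error about 25,000 |

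In the third row every patient coded 1 has dengue, so secondary cases contribute nothing to the symptom estimate. What remains is primary dengue versus non-dengue:

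- All dengue: (0.40/0.60) / (0.20/0.80) = 2.67
- Primary only: (0.30/0.70) / (0.20/0.80) = 1.71

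A simulation of 400,000 patients gave 2.63 and 1.66, in line with these values.

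**Symptom as the dependent variable.** The article's wording also allows this direction. Missing values again leave only dengue patients. With a not-applicable level, the dengue indicator equals 1 minus the indicator of that level, so the two cannot be separated. Coding 0 for non-dengue is estimable, but the dengue coefficient is again primary dengue versus non-dengue (1.66 in the same simulation).

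**Without the covariate.** With primary/secondary and inpatient status both left out, large simulated runs returned 2.63 to 2.74 against the true 2.67.

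**Inpatient status.** Let p(s,d) be the admission probability for symptom s and dengue d, with logit p = a + bs·s + bd·d. Within inpatients the symptom odds ratio is the true one times

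p(1,1)·p(0,0) / [p(1,0)·p(0,1)].

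Take a true odds ratio of 3, bs = 2 and bd = 1 (all assumed):

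- a = −3: 3 × (0.500 × 0.0474) / (0.269 × 0.119) = 2.22
- a = −5: 3 × (0.119 × 0.00669) / (0.0474 × 0.0180) = 2.81

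With bd = 1.5 the values are 1.81 and 2.64. The intercept −3 corresponds to about 28% to 37% of dengue patients admitted, and −5 to about 6% to 10%, if the symptom occurs in 20% of non-dengue patients. At −6 the range is 2.92 to 2.85, and at −2 it is 1.94 to 1.55. If admission depends on only one of symptom and dengue, with no interaction, there is no material change. Under this additive logit model the outpatient stratum has the same odds ratio as the inpatient stratum, so stratifying reproduces the adjusted value exactly.

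**The case against.** **The list is illustrative.** It is open-ended and stands in a condensed article that fixes no coding or missing-data rule; the covariate lists of two analyses may have been merged. That is plausible. But the covariate is named expressly for this contrast, and no coding makes it work there. If it was meant for the dengue-only models, the text still needs the same edit.

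**Past exposure could be defined for everyone.** IgG is tested in enrolled patients, and Table 1 includes self-reported previous dengue. This is true, but prior exposure is a different variable from the one named.

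**The failure announces itself.** This holds for the missing and not-applicable codings, which break on the first run, and it limits the harm. It does not hold when the symptom is the dependent variable and non-dengue patients are coded 0: that model converges and reports an odds ratio for primary dengue under a label covering all dengue.

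**A stronger reading of inpatient status.** A reader might infer that inpatient status is plainly a consequence of symptoms and of the RDT result, so that adjusting for it shrinks the odds ratios by a known amount. The documents do not support this. Table 1 records department of enrolment separately from the visit outcome, so the covariate may be the setting. Facility types differ by site: primary healthcare centres in Burkina Faso, one hospital in Gabon, a dispensary and hospitals in Kenya. Nothing says that admission follows the RDT result; the test is done on patients already enrolled. No admission rate is given, and the size of any bias turns on it.

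**Conclusion.** Wrong as written for primary versus secondary infection. The conclusion follows from the definition of the variable and does not depend on the assumed dengue share or symptom frequencies, which only illustrate the size. The model as specified either cannot be fitted or answers a narrower question, primary dengue versus non-dengue. Under the assumed frequencies that gives 1.71 in place of 2.67.

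Inpatient versus outpatient status is a secondary and debatable point. It may be partly a consequence of symptoms and disease and partly the enrolment setting. Under the assumptions above the bias runs from negligible to substantial, and the article does not allow it to be narrowed. It is not shown to be an error.

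**What to change.** In Planned statistical analysis, delete primary versus secondary infection from the covariates of the dengue versus non-dengue model and keep age and days since fever onset. State that primary versus secondary status is used only in models within confirmed dengue (by age, serotype and severity).

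For care setting, at most make the model without inpatient status the main result and report the model adjusted for it as a sensitivity analysis, saying whether the variable is department of enrolment or visit outcome. Inpatient and outpatient strata should not be offered as a remedy for bias, since they condition on the same variable.

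The cost is analysis wording only, with no new data and no change to sample size.
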